### Design and groups

2.3

The study design of this bicentric, prospective, randomized, controlled, interventional trial is visualized in **Figure 1**, and procedures are described in detail in subsequent sections. Female patients are randomized into three groups before undergoing gynecological laparoscopic surgery. Randomization is accomplished prior to the personal interview with the study physician. To randomize the patients, we use block randomization with random distribution to ensure a balance in sample size across groups over time and the ability to perform interim analysis. Stratification is performed within the Hamburg and Essen clinic locations.

**Figure 1 f1:**
[figure not shown]
Graphical overview of the study schedule. OLP, open-label placebo; OP, operation; preop, preoperative; PACU, post anesthesia care unit; T, time point. OLP+V, open-label placebo + video.

Study group 1 receives the OLP with a positive rationale conveyed by a study physician (OLP-Group; for details see 3.4.1). We will use white pills (P-Tabletten weiß 10 mm Lichtenstein, Zentiva Pharma GmbH, Frankfurt, Germany) as Open-Label Placebo pills. To test effects of social observational learning aspects, study group 2 receives the identical treatment as group 1, and additionally watches a video showing a patient who receives OLP treatment and reports to be highly satisfied with its effects on preoperative anxiety (OLP+V-Group; for details see 3.4.1.1). A third group undergoes the standard care (“treatment as usual”, TAU-Group). Of note, patients are not always given medication to reduce anxiety in standard care. However, it is standard procedure in both clinics for patients to be given a benzodiazepine on request or if they report severe concerns or anxiety. Side effects and contraindications will be considered and discussed with the patients. If a benzodiazepine is prescribed, its standard dose is 7.5 mg Midazolam p.o., only if the patient weighs less than 50kg a reduction in dose will be accomplished. In the OLP-Group, patients receive the OLP first and the anxiolytic only if they still require it afterwards, which will be documented and considered in analysis. The impact of anxiolytic medication on the results of the study will be specifically analyzed to determine whether its inclusion or exclusion from the dataset affects the results, ensuring a careful assessment of its impact on the overall effectiveness of the OLP.

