### Data analysis

2.7

A power analysis calculated with G*Power (version 3.1.9.6) resulted in a sample size of 120 patients for an expected small to medium effect size f of 0.2, two measurement time points, three groups, a significance level of α=0.05 and a power of 0.95. In order to be able to take possible exclusions during the course of the study into account, 20% more patients will be recruited, so that the final sample size is N=144 women. The effect size was derived from our own data and the literature after careful consideration with experts and colleagues at the two university hospitals. A medium to small effect size was chosen in order to be able to investigate small effects.

To analyze the main outcome (object 1), preoperative anxiety (APAIS), we will perform a univariate analysis of variance (ANOVA) with *post hoc* tests to determine differences in anxiety before surgery in the three groups. To analyze the dynamic changes of anxiety in the different groups before and after open placebo administration (TAU, OLP and OLP-V), repeated measures analyses of variance followed by *post hoc* tests are performed (object 2). In addition, ANOVAs will be conducted to assess postoperative pain (NRS) and other clinical characteristics by group (object 3). Patient and staff reports are primarily analyzed descriptively and free-text qualitatively (object 4). Furthermore, correlation and regression analysis will be used to identify exploratory predictive patient characteristics (object 3 & 4). No interim analysis is planned. If data is only available from one patient at three or fewer time points, the patients are excluded from the analysis.

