**Figure 2 f2:**
[figure not shown]
Graphical overview of the expected results. TAU, treatment as usual; OLP, open-label placebo; OLP+V, open-label placebo + video.

Objective 1: To compare preoperative anxiety after standard treatment (TAU-Group) against modulation of treatment expectations using OLP (OLP-Group) and to determine whether the effects after modulation of treatment expectation using OLPs can be enhanced by a video with aspects of verbal suggestion and observational learning (OLP+V-Group).

We postulate a lower level of preoperative anxiety in the OLP groups compared to treatment as usual, e.g. the provision of information as part of the anesthesiological consultation, with the greatest effects in the OLP+V-Group (**Figure 2**). Therefore, we analyze the self-reported preoperative anxiety (APAIS), to determine differences in anxiety immediately before surgery across the three groups. Previous studies, such as those by Schaefer et al. (30, 59), and Buergler et al. (60), demonstrate the effectiveness of OLP in modulating negative emotions, such as anxiety and stress (30, 59, 60). In a study with test anxiety as the primary outcome, Schaefer et al. demonstrated how the use of OLPs could successfully contribute to its reduction in students (30). The same working group presented that self-reported lower emotional distress when viewing highly arousing negative pictures in the OLP-Group was associated with activation of brain regions known to modulate affective states, such as the hippocampus and periaqueductal grey (59). In turn, a positive correlation between anxiety and OLP response has already been shown, with gastrointestinal-specific anxiety beeing a predictor of response to OLPs in patients with irritable bowel syndrome (38). Therefore, we expect a reduced level of preoperative anxiety in the OLP groups. It should be noted, that the literature does not indicate the minimum clinically significant difference for the APAIS or anxiety on an NRS, therefore it should be considered that a statistically significant result does not necessarily imply clinical significance.

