In addition to reduced anxiety, we expect that patients in the OLP-Group will require less benzodiazepine rescue medication. In the postoperative period, we expect patients in the OLP groups to report less pain than those in the TAU-Group. A difference of at least 1 point on the NRS is considered a clinically relevant difference, as the MCID for acute pain management is based on a systematic review of at least 8 mm on a VAS scale (62). Our assumption is based on the close relationship between anxiety and pain (8, 9). In particular, visceral pain is associated with anxiety and negative emotions (63), leading us to hypothesize that visceral pain will be particularly reduced with OLP. Exploratively, we will examine analgesic consumption in the PACU and postoperatively on the ward, as reduced preoperative anxiety may be associated with reduced postoperative opioid consumption. We also aim to assess whether there are group differences in patients’ reported self-efficacy and the appropriateness of placebo use in the clinical context from the patient’s perspective.

Objective 4: To explore the patient and healthcare providers perspective regarding the use of OLPs to reduce anxiety before surgery.

Research on open-label placebo in the clinical context remains novel, meaning there is little data on the patient and healthcare provider perspective. To date, quantitative research in clinical populations is lacking and the healthcare provider perspective, e.g. those who administer OLPs, has not yet been captured (43, 44, 64).

Therefore, one aim of this study is to explore patients’ views on the effectiveness and appropriateness of OLPs before surgery in a large clinical population. Firstly, we investigate the effectiveness of OLPs from the patient’s perspective post-surgery. We further intend to gain an understanding of whether patients consider OLP administration to be critical in the context of surgery or are open to it, thus asking their opinion on the application in this and other situations. In addition, we plan to interview the TAU-Group who have not received OLPs for their views on the application of OLPs. In addition to the patient perspective, we include the health care providers opinion on patients’ benefit from taking OLPs.

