Furthermore, it cannot be excluded that simply showing a video after explaining the study and the rationale has an anxiolytic effect, regardless of the content. However, it proved difficult to find a truly neutral video to show before surgery, as patients are particularly vulnerable at this time. The concept of a “neutral” video in this context is problematic; almost any content could be unintentionally distracting or, more worryingly, potentially induce nocebo effects. After careful consideration, we decided not to include such a video in our trial. To minimize any “dose” effect of the additional video exposure, the study physician leaves the room after the OLP briefing and a trained assistant then starts the video. The findings of studies on the influence of a video as part of information on the perioperative anxiety experience of patients are heterogeneous, but a video does not appear to contribute per se to a reduction in anxiety in patients compared to patients without watching a video (66). In addition, there is so far little knowledge and data regarding the content of a treatment expectation optimizing and anxiety reducing video. Consequently, a possible influence of verbal suggestion and observational learning on the effect of OLPs needs to be carefully interpreted.

Our study population consists exclusively of female participants, who have a higher prevalence of preoperative anxiety, but as a result we can only make limited general statements about preoperative anxiety. Another limitation is that our treatment-as-usual (TAU) group as control does not allow us to make a clear statement about the effectiveness of any prescribed anxiolytic medication and compare it with the effect of OLP.

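### Comparing results with and without anxiolytic users cannot show whether anxiolytics affected the OLP result, because use arises after randomisation under a rule that differs by arm

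*Protocol article*

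**What the plan says.** Section 2.3 (Design and groups) sets the anxiolytic rules. In standard care at both clinics, patients are "given a benzodiazepine on request or if they report severe concerns or anxiety". In the OLP group, "patients receive the OLP first and the anxiolytic only if they still require it afterwards, which will be documented and considered in analysis". OLP+V is described as the same treatment plus a video, so the OLP-first rule is taken to apply there too.

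The same section says the medication's impact will be "specifically analyzed to determine whether its inclusion or exclusion from the dataset affects the results", and adds the purpose: "ensuring a careful assessment of its impact on the overall effectiveness of the OLP".

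Four other places bear on this:
- Section 2.7 (Data analysis) defines the main analysis as an ANOVA of APAIS across the three groups. It names one exclusion: "If data is only available from one patient at three or fewer time points, the patients are excluded from the analysis". Anxiolytic use is not a ground for exclusion.
- Section 3, Objective 1, gives the aim of that analysis as "to determine differences in anxiety immediately before surgery across the three groups".
- Section 3, Objective 3, expects that "patients in the OLP-Group will require less benzodiazepine rescue medication".
- Section 4.1 concedes that the TAU control "does not allow us to make a clear statement about the effectiveness of any prescribed anxiolytic medication".

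**The concern.** The plan names a method (see whether results change when the anxiolytic is included or excluded) and the conclusion to draw from it (the anxiolytic's impact on OLP effectiveness). Four features of the design break the link between them:

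- Randomisation precedes the study physician's interview, typically one to five days before surgery. In the OLP arms the drug can come only after the pill, about 45 minutes before surgery, so intake there is a post-randomisation event.
- Intake is triggered by anxiety, which is what the primary outcome measures.
- The trigger differs by arm: a request or severe anxiety in TAU, persisting need after the pill under OLP.
- The investigators themselves expect treatment to lower use.

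Removing users therefore takes anxious patients out of each arm at different rates and by different selection, and the remaining groups are no longer comparable by randomisation. A reader would naturally take two agreeing results as reassurance and two differing results as a drug effect. Either reading can be wrong.

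**Working it through.** The plan states no figure to reproduce, and no anxiolytic rate, drug effect or APAIS SD. The usage and correlation inputs below are assumptions; the arm size comes from section 2.7 (120 analysed patients ÷ 3 arms = 40).

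**Assumed inputs**
- p, proportion using an anxiolytic in TAU: 0.10–0.40
- k, OLP use as a fraction of TAU use: 0.25–1
- rT and rO, correlation between need for the drug and the untreated anxiety rating in TAU and OLP: 0.3–0.7, set separately because the rules differ
- No OLP effect and, unless stated, no drug effect

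**Shift caused by excluding users.** If the patients highest on need take the drug, the mean rating of those left in an arm with use q falls by r × L(q), where L(q) = φ(z_q)/(1 − q) and z_q is the upper-q normal quantile. The OLP minus TAU contrast after exclusion is then

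shift = rT × L(p) − rO × L(kp), in SD units, positive meaning against OLP.

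L(0.10) = 0.195, L(0.15) = 0.274, L(0.30) = 0.497, L(0.40) = 0.644.

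| p | k | rT | rO | Shift (SD) |
|---|---|---|---|---|
| 0.3 | 0.5 | 0.5 | 0.5 | 0.5 × (0.497 − 0.274) = +0.11 |
| 0.3 | 0.5 | 0.3 | 0.7 | 0.149 − 0.192 = −0.04 |
| 0.3 | 1 | 0.3 | 0.7 | −0.4 × 0.497 = −0.20 |
| 0.4 | 0.25 | 0.7 | 0.3 | 0.451 − 0.059 = +0.39 (grid maximum) |
| 0.4 | 1 | 0.3 | 0.7 | −0.4 × 0.644 = −0.26 (grid minimum) |

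Simulation with 2 million patients per arm agrees with these to within 0.002 SD. The all-patients contrast stays within 0.002 of zero.

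**Disagreement without a drug effect.** In the first row the all-patients contrast is 0 and the contrast after exclusion is 0.11 SD, although neither OLP nor the drug does anything.

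**Agreement despite a drug effect.** Let the drug lower the rating by m = 0.3 SD in users, with p = 0.3, k = 0.5, rT = 0.40, rO = 0.56:
- All patients: p(1 − k)m = 0.3 × 0.5 × 0.3 = 0.045 SD against OLP.
- Users excluded: 0.40 × 0.497 − 0.56 × 0.274 = 0.045 SD against OLP.

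The two versions match although the drug works and causes the whole all-patients difference.

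**A different model gives the same answer.** Latent anxiety has SD 1 and noise SD 0.6, and the drug is taken above an arm-specific threshold (units: SD of latent anxiety).
- Neither treatment effective, different thresholds: 0.00 in all patients, 0.15 to 0.24 against OLP after exclusion.
- Drug effect 0.5, no OLP effect, same threshold: both contrasts 0.00.
- True OLP benefit 0.40, same threshold: the contrast after exclusion is a benefit of 0.29 whether the drug effect is 0 or 0.5.

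**False rejection.** Three-arm ANOVA at nominal 5%, 40 randomised per arm, OLP+V behaving like OLP, no effects: about 5% with all patients. After exclusion it rejects in 7% (0.11 SD case), 12% (0.20 SD case), 15% (0.26 SD extreme) and 31% (0.39 SD extreme).

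**Covariate reading.** If inclusion or exclusion means adding anxiolytic use as a model term, the arm coefficient under no effects is 0.13 SD at p = 0.3, k = 0.5, rT = rO = 0.5, and 0.12 SD at rT = 0.3, rO = 0.7. It is 0 when use is equal across arms.

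**The case against.** The strongest reply is that this is a supplementary check. Section 2.7 does not drop anxiolytic users from the primary ANOVA, so the main result is untouched. That is correct, and it limits the severity. Taken literally, the plan only promises to see whether results change, which the comparison can do. But the sentence goes on to say what the check secures, namely an assessment of the drug's impact on OLP effectiveness, and that does not follow.

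Section 4.1 is some mitigation, since it admits that TAU cannot show whether anxiolytics work or how they compare with OLP. It says nothing about selection created by removing users and leaves the section 2.3 claim in place.

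The timing of prescribing in TAU is not stated. A request could arise at the ordinary anaesthesia consultation, before study information is given. That would not remove the problem, because intake in the OLP arms still depends on need after the pill.

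The sizes are assumed and the extremes need extreme inputs. At 10% use in TAU and 5% under OLP with r = 0.5 in both arms, the shift is only 0.5 × (0.195 − 0.109) = 0.04 SD. The plan also excludes acute severe anxiety episodes and long-term benzodiazepine users, which may keep use low. If use is rare the bias is small, but the comparison still does not answer its question.

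Finally, with lower use under OLP and similar selection in both arms, exclusion works against OLP, so a surviving benefit would be some reassurance. That rests on similar selection, which the OLP-first rule gives reason to doubt: patients who still need the drug after the pill may be more strongly selected on anxiety.

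**Conclusion.** The concern holds. The with/without comparison cannot show whether anxiolytics affected the OLP result, whether it is read as excluding users or as adjusting for use. This conclusion follows from the design and does not depend on the assumed rates.

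The size does depend on them: from 0.26 SD in favour of OLP to 0.39 SD against it over the stated grid, and 0.11 SD against OLP in the mid-range case. The direction cannot be known from the document. Bias runs against OLP if users differ between arms mainly in number, and can favour OLP if OLP users are more strongly selected on anxiety.

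The primary all-patients ANOVA is not biased by this. It validly estimates OLP first with rescue anxiolytic versus usual care. What needs correcting is the conclusion promised from the supplementary analysis.

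**What to change.** 1. In section 2.7, state that the primary ANOVA keeps every randomised patient regardless of anxiolytic use, and that it estimates OLP first with rescue anxiolytic versus usual care.
2. In section 2.3, remove the claim that the with/without comparison gives a careful assessment of the anxiolytic's impact. Either drop the exclusion analysis, or label it descriptive and subject to selection, with no conclusion drawn from agreement or disagreement. Treat adjustment for use the same way.
3. Beside the primary result, report by arm how many patients received an anxiolytic and when, relative to the APAIS rating.

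The cost is wording in two sections and one table. Section 2.3 already says use in the OLP group is documented, and section 2.5.7 records preoperative sedatives; only timing relative to the rating may need adding. Sample size, randomisation and procedures do not change. The price is that the effect of OLP in the absence of anxiolytics is not estimated, but the planned comparison would not have estimated it either.

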### Study procedures

2.4

Patients undergoing elective gynecological laparoscopy at the University Hospitals of Hamburg and Essen are offered to participate in the study. After consultation with an anesthesiologist who is not involved in the study, patients are informed about the study, clinically examined and informed consent is obtained by a study physician, an experienced anesthesiologist. In all groups, information about the study is provided by the study physicians in the premedication outpatient clinics individually, which is typically one to five days before the surgery at both study sites.

Patients are assessed at 5 predefined time points. After informed consent, patients complete a comprehensive questionnaire battery (T1). This package includes information on demographics, state and trait anxiety, pain level over the past 4 weeks, treatment expectations regarding to the upcoming surgery and, if applicable, expectations concerning OLP (for details see 3.5). Patients will complete a short questionnaire at the beginning and at the end of the consultation with the study physician, about their current anxiety and treatment expectations in order to assess the impact of the study physician’s suggestions, including the rationale for OLP. Additionally, the patients rate the warmth and competence of the study physician using a standardized questionnaire. Patients in the OLP+V-Group watch the video after the consultation with the study physician and are also subsequently asked to answer questions about their perception of the video.

At the time the patients are called to the operating room, approximately 45 minutes before the start of surgery (T2), patients randomized to the OLP groups receive OLPs from the nursing staff. In addition, the patients evaluate their preoperative anxiety. Just before the induction of anesthesia in the preoperative phase (T3), preoperative anxiety is assessed again. In addition, the anesthetist subjectively assesses the patients’ level of calmness or anxiety. After surgery in the recovery room, patients are asked about their current level of anxiety and about their current pain level for visceral and somatic pain modalities (T4).

On the first postoperative day (T5), patients report if they took the OLPs, their current anxiety and retrospectively their anxiety before surgery. They assess mobility and their general condition. Current pain, visceral and somatic pain modalities as well as discomfort are also recorded. In addition, the warmth and competence of the anesthesiologist performing anesthesia in interacting with the patient and the patient’s perspective on the acceptability of OLPs is recorded.

The patients in the TAU-Group also receive the questionnaires at the same time points, and otherwise no differences from standard care are made. Patients can withdraw their participation in the study at any time.

#### Treatment instruction

2.4.1

Depending on the intervention group, participants receive appropriate written and verbal treatment information, and sign distinct versions of consent forms. The TAU-Group receives *consent form version A*, explaining the participation in a questionnaire study on preoperative anxiety. The two OLP groups receive *consent form version B*, explaining the use of an OLP to support well-being and to reduce anxiety before surgery. In version B, the possibility is mentioned that the patients will additionally be shown an information video.

All treatment-related information is provided by the study physicians (authors [name] and [name], respectively) according to a highly standardized protocol. For OLP instruction groups, the rationale protocol is based on a previously used approach of positive framing with the aim of optimizing placebo response (26). In addition, we considered studies of patient perspective on OLPs (43, 44) and obtained feedback from non-participating patients. Established communication strategies were adopted from previous reports (18), including warm and empathic interactions and supporting self-efficacy expectations about the ability to effectively cope with adverse symptoms, particularly anxiety. Key instructional points of the OLP rationale protocol include awareness that placebo effects are powerful and have been shown to have effects that can be similar to those of analgesics (**Supplementary Table 1**). We also explain that doubts are not a problem as OLPs can be effective through conditioning, context and observation. Furthermore, we point out that patients compliance is critical and that placebos can unlock the body´s natural healing power (45).

